**Fig. 2 Fig2:**
[figure not shown]
Hybrid implementation-effectiveness study design

#### Early Arm health systems

##### Eligibility criteria

Eligible healthcare systems are those that provide care to female smokers and are in the Appalachian region of the target states. Eligible providers in the healthcare systems are those who are directly involved with patient care (e.g., physicians, advance practice professionals). Eligible patients include women who are: (1) age 18 to 64; (2) smokers who consume at least five cigarettes per day; (3) ready to quit smoking within the next 6 months; (4) English-speaking; (5) able to participate in phone counseling; (6) willing to try pharmacotherapy; and (7) not pregnant.

##### Procedures

The study design procedures of *Break Free* include: (1) training providers, Clinic Champions, and Enrollment Specialists as described above; (2) recruitment and consent of potential participants; (3) provision of cessation counseling and pharmacotherapy; (4) billing for services; (5) fidelity assessments; (6) follow-up assessments; and (7) cost-effectiveness assessments. All study protocols were developed with and reviewed by a Community Advisory Board, External Scientific Advisory Board, and Data and Safety Monitoring Board.

Trainings: As previously described, all providers from participating clinics who are directly involved in patient care will be trained in *Break Free* and the AAR method. Trainings will take place in-person or virtually. The training materials were adapted from Rx for Change^®^, an organization that disseminates public use smoking cessation resources for healthcare providers [40]. In addition, providers will receive pocket cards (see Additional file 1) to remind them of *Break Free* eligibility criteria and pharmacotherapy options for smoking cessation.

All who attend the provider training will be asked to complete a consent form and pre-training assessment. Questions focus on attitudes, confidence, and practices around evidence-based smoking cessation treatment; knowledge of counseling and pharmacotherapy for smoking cessation; and demographics. Immediately after the provider training session, all participants who provided consent and completed the pre-training survey will be asked to complete a post-training survey to assess increased knowledge following the training. Provider surveys will also be distributed at the end of the implementation phase, with similar questions as the baseline survey plus items to assess acceptability and satisfaction with AAR models and *Break Free* specifically. Providers who complete virtual trainings will be sent a link to an online informed consent prior to completing an online survey.

Recruitment, Enrollment, and Consent of Participants: Figure 3 outlines the process for participant recruitment and enrollment into the early arm intervention. Eligible patients will be identified during routine clinic visits. Providers will ask patients about tobacco use and advise smokers to quit. Women who are interested in quitting within the next 6 months and are eligible for *Break Free* will receive a prescription for pharmacotherapy and referral to the Enrollment Specialist for that clinic or health system. The Enrollment Specialist will introduce potential participants to the *Break Free* program, distribute the patient educational materials, and collect patient contact information for referral to the study-specific TTS to be consented into the study.

Within a week, the study-specific TTS will contact potential participants and obtain verbal informed consent. If the TTS is unable to reach the potential participant, they will attempt to reach them up to ten times to schedule the informed consent and baseline assessment. Consented participants’ contact information is entered into RedCap data management system for secure storage. Contact information is used to connect participants to *Break Free* phone counseling calls and for follow-up assessments. All participants are assigned a subject ID, which is stored in RedCap independently from participant data. After consent is obtained, the study specific-TTS will administer the baseline assessment via phone. Participants will receive $10 for completing the baseline assessment.

Counseling and pharmacotherapy: The *Break Free* 4-session counseling protocol begins after the baseline assessment is complete. The study-specific TTS will counsel participants from health systems that do not have a dedicated TTS on staff; otherwise, the health system’s TTS will perform the counseling. Again, if the TTS is unable to reach participants for a counseling session, they will call them up to ten times to reschedule. If a participants’ phone number is not working, then the TTS will send a follow-up email and, if needed, a mailed letter, to update participant contact information.

Fidelity assessments: Fidelity to the intervention by providers and the TTS will be assessed separately. To assess provider fidelity to the AAR model, each quarter during a 1-week period, all patients who visit the clinic will be asked to complete an anonymous, self-report, post-provider visit survey. Paper surveys will be collected in a sealed envelope by the check-out staff person at the clinic and mailed to the study team by the Clinic Champion. Patients will also have the option to complete an online survey by scanning a QR code.

To assess TTS fidelity to *Break Free*, ten percent of all *Break Free* participants will be randomly selected and called after a scheduled counseling call to confirm the call occurred and to determine which content was discussed. No financial or other incentives are given for the fidelity assessments.

Patient follow-up assessments: *Break Free* participants will be contacted at 3-, 6-, and 12-months post enrollment to assess current tobacco use and quit attempts via online or phone surveys. Participants will receive a $10 gift card incentive for completion of each follow-up survey. Two weeks prior to each follow-up survey, participants will be sent a proactive reminder email or mailed letter reminding them of the upcoming follow-up assessment.

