#### Delayed Arm health systems

While the Early Arm health systems are in the Early Intervention phase, the Delayed Arm health systems will continue usual care (Fig. 1). During this phase, to determine “usual care” tobacco-related outcomes in the Delayed Intervention arms, providers will ask eligible female smokers about their tobacco use and assess readiness to quit. Female smokers who are interested in quitting in the next 6 months will be asked to participate in this observational component of the study. Those who agree to participate will be given either a paper a baseline survey packet with a consent script to sign and the baseline survey in the clinic, where they will be asked to complete it in the clinic and then mail it to the research team (a self-addressed stamped envelope will be included), or an online link with an electronic consent and survey. The consent will include language about follow-up surveys at 3, 6, and 12 months. Study staff will call or email Delayed Arm participants at 3-, 6-, and 12-months post-baseline to assess smoking behaviors. Participants will receive a $10 gift card incentive for completion of each survey. Once Delayed Arm clinics begin the Active Intervention phase, they will follow all procedures implemented in Early Arm health systems as described above.

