#### Patient outcomes

For all patient outcomes, we will conduct ITT analyses. We will assume that non-responders to surveys will be continued smokers.

Hierarchical (mixed) models will be used to compare smoking cessation outcomes at 6- and 12-months between female smokers in the Early and Delayed Arm health systems. Logistic models will be used for the binary outcomes, including the point prevalence, floating and prolonged abstinence, and at least one 24-h quit attempt. Subsequent analyses will adjust for patient-level characteristics in comparing smoking cessation at 6 and 12 months among patients in the Early and Delayed Arm health systems.

Mixed models will be used to assess measures of participant satisfaction with *Break Free*, using random effects for health system and primary provider. Subsequent analyses will add patient characteristics in order to evaluate whether satisfaction with the *Break Free* program differs by these characteristics.

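### The two-week advance reminder is written for Break Free women only, so follow-up effort differs by arm as written, and the rule that non-responders are smokers can turn any resulting response gap into a quit-rate gap

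*Protocol article*

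**What the plan says.** Early Arm, Procedures. Break Free participants are surveyed at 3, 6 and 12 months, online or by phone, with a $10 gift card for each survey. The section adds: "Two weeks prior to each follow-up survey, participants will be sent a proactive reminder email or mailed letter".

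The same section has contact rules for the tobacco treatment specialist (TTS) during counselling: "if the TTS is unable to reach participants for a counseling session, they will call them up to ten times to reschedule". If the phone number does not work, "then the TTS will send a follow-up email and, if needed, a mailed letter, to update participant contact information". Contact details are held for "phone counseling calls and for follow-up assessments".

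Delayed Arm health systems. The usual-care women are followed under a separate description: "Study staff will call or email Delayed Arm participants at 3-, 6-, and 12-months post-baseline to assess smoking behaviors". The $10 gift card per survey is repeated here. No advance notice or contact-detail update is described. The paragraph ends: "Once Delayed Arm clinics begin the Active Intervention phase, they will follow all procedures implemented in Early Arm health systems as described above".

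Study design. The usual-care cohort is the comparison group for effectiveness.

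Statistical analyses. Under Patient outcomes: "We will assume that non-responders to surveys will be continued smokers". Under Missing data, missing outcomes are instead to be filled by multilevel multiple imputation, with intervention group and health system in the model.

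**The concern.** The effectiveness comparison sets Early Arm women against Delayed Arm women in the usual-care phase. Staff who follow the text would send an advance email or letter before each survey in one arm and not in the other. The sentence that makes procedures common takes effect only after the comparison phase, so it does not close the gap.

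The TTS contact-updating step belongs to counselling, not to the surveys. Because the same contact details serve both purposes, it may still help Early Arm follow-up indirectly.

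If every non-responder is scored as a smoker, each arm's observed quit rate depends on response as well as on abstinence. Lower response in usual care would then count in favour of Break Free. Participants are unblinded and outcomes are self-reported, so equal follow-up effort is one safeguard that the sponsor can control.

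**Working it through.** **Inputs from the protocol article (Sample size and power analysis).** Quit rates 10% and 25%; intraclass correlation 0.017; 10 health systems, 5 per arm; 43 evaluable and 51 enrolled smokers per system; two-sided 5%; one dropout figure of 20%, not split by arm.

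**Assumptions, because the document gives no response rate by arm.** Response of 80–90% in the Early Arm and 60–80% in the Delayed Arm; response unrelated to quitting.

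**The plan's own figure.** For 10% v 25%, individual randomisation needs 100 per arm. With design effect 1 + (m − 1) × 0.017 and an allowance of one cluster per arm (4 effective clusters), m = 100 × (1 − 0.017) / (4 − 100 × 0.017) = 98.3 / 2.3 = 42.7, which rounds to the stated 43. A t-test on 8 degrees of freedom at m = 43 gives 79.7% power. The stated figure reproduces, and this concern does not change it.

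**Effect of the non-responder rule.** Observed rate = true rate × response. With the same true rate p in both arms, the false difference is p × (response in Early − response in Delayed).

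Rejection uses SE = √{[e(1 − e) + d(1 − d)] × DE / 255}. Here e and d are the observed Early and Delayed rates, DE = 1 + 50 × 0.017 = 1.85, and 255 = 5 × 51. The test is a noncentral t on 8 degrees of freedom with critical value 2.306.

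Example, p = 15%, response 85% v 70%:
- e = 0.15 × 0.85 = 0.1275 and d = 0.15 × 0.70 = 0.105, a difference of 0.0225
- SE = √[(0.1112 + 0.0940) × 1.85 / 255] = 0.0386
- noncentrality = 0.0225 / 0.0386 = 0.58
- two-sided rejection = 8.1%

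No true effect, p = 15% in both arms:

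| Response, Early v Delayed | Observed rates | False difference | Rejection (nominal 5%) |
|---|---|---|---|
| 85% v 80% | 12.75% v 12.0% | 0.75 points | 5.3% |
| 85% v 75% | 12.75% v 11.25% | 1.5 points | 6.3% |
| 85% v 70% | 12.75% v 10.5% | 2.25 points | 8.1% |
| 90% v 60% (extreme) | 13.5% v 9.0% | 4.5 points | 18.2% |

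At 20% true abstinence, 85% v 70% gives 9.4% and 90% v 60% gives 23.5%.

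Design rates, true 25% v 10% (difference 15 points, odds ratio 3.00):

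| Response, Early v Delayed | Observed rates | Difference | Odds ratio |
|---|---|---|---|
| 80% v 80% | 20% v 8% | 12 points | 2.88 |
| 80% v 70% | 20% v 7% | 13 points | 3.32 |
| 80% v 60% | 20% v 6% | 14 points | 3.92 |
| 70% v 80% (gap reversed) | 17.5% v 8% | 9.5 points | 2.44 |

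The planned models are logistic, so the odds ratio is the measure affected. At 80% v 60% the odds ratio exceeds its true value while the absolute difference stays below its true value.

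**The case against.** The article condenses a fuller protocol and never says that usual-care women get no reminder. Reminder schedules are the kind of detail an article may leave out. This stands in part: the full protocol may already treat the arms alike. But the article gives the reminder's timing and mode for one arm, describes the other arm's follow-up separately while repeating the time points and incentive, and dates when procedures become common. That is a stated difference, not only a silence.

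A reader might also infer more than the text supports:

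- **That response will differ by arm.** No arm-specific response is given. Usual-care women enter by completing a consent and survey themselves, which may select good responders, so the gap could be small or reversed.
- **That the ten calls and contact tracing are survey procedures denied to usual care.** They are written for consent, baseline and counselling. No such rule is stated for the follow-up surveys in either arm.
- **That gaps of 15 or 30 points should be expected.** Nothing suggests that one reminder moves response that far. A gap of 5 to 10 points gives about 5.3% to 6.3% rejection at 15% abstinence.
- **That the effect is inflated on every scale.** In the design case with 80% v 60% response, the absolute difference is 14 points against a true 15.
- **That the non-responder rule is the only one in play.** The Missing data section plans multiple imputation, under which this mechanism would not act in the same way.

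**Conclusion.** The point holds in conditional form. As written, follow-up effort differs by arm in the phase that supplies the effectiveness comparison, and the clearly stated difference is the advance reminder. If usual-care response is lower as a result, the non-responder rule shifts the odds ratio, and the false-positive rate under no effect, toward Break Free.

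The likely size is modest. Response gaps of 5 to 15 points at 15% abstinence give false differences of about 0.75 to 2.3 points and rejection of about 5.3% to 8%; 18% needs an extreme gap. These figures rest on assumed response rates, on response unrelated to quitting, and on the non-responder rule governing rather than imputation. The documents do not show that a gap will occur. The change is still worth making, because the source of bias is avoidable and cheap to remove.

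**What to change.** State one follow-up survey procedure and apply it to both arms, in the Early Arm Procedures section and in the Delayed Arm section for the usual-care phase. It should give the same two-week advance email or letter, the same survey contact attempts, the same contact-detail update steps and the same modes at 3, 6 and 12 months. Counselling calls stay as part of the intervention.

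Report survey response by arm at each time point. Reconcile the Missing data section with the Patient outcomes section, so that one rule for missing abstinence is primary and any other is labelled a sensitivity analysis.

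Cost: about 255 extra emails or letters per time point (half of 510) and a short edit. No sample-size figure changes. If the full protocol already applies the reminder to both arms, one sentence in the Delayed Arm section settles that part.

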#### Delayed Arm health systems

While the Early Arm health systems are in the Early Intervention phase, the Delayed Arm health systems will continue usual care (Fig. 1). During this phase, to determine “usual care” tobacco-related outcomes in the Delayed Intervention arms, providers will ask eligible female smokers about their tobacco use and assess readiness to quit. Female smokers who are interested in quitting in the next 6 months will be asked to participate in this observational component of the study. Those who agree to participate will be given either a paper a baseline survey packet with a consent script to sign and the baseline survey in the clinic, where they will be asked to complete it in the clinic and then mail it to the research team (a self-addressed stamped envelope will be included), or an online link with an electronic consent and survey. The consent will include language about follow-up surveys at 3, 6, and 12 months. Study staff will call or email Delayed Arm participants at 3-, 6-, and 12-months post-baseline to assess smoking behaviors. Participants will receive a $10 gift card incentive for completion of each survey. Once Delayed Arm clinics begin the Active Intervention phase, they will follow all procedures implemented in Early Arm health systems as described above.

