### Hybrid effectiveness-implementation study design

In this cluster randomized trial, health systems are stratified by state and then randomized in a 1:1 ratio to either an Early Arm or Delayed Arm. To reduce the risk for contamination, within each stratum, health systems are randomized into Early Intervention or Delayed Intervention arms. All clinics within each health system are randomized to the same condition (Early or Delayed Intervention). Neither health systems nor study participants are blinded to their intervention assignment.

Figure 2 outlines the timeline for study implementation and evaluation. Following a planning phase (months 1–23; not shown in the figure), *Break Free* will be implemented in Early Arm health systems over a 12-month period. After this 12-month period ends, research staff will train Early Arm health systems on how to bill for brief counseling (AAR) and smoking cessation phone counseling, as well as how to implement *Break Free* using their own staff and resources as they transition to a full sustainability period. During this period, Early Arm health systems will also learn how to “bundle” all three *Take CARE* projects addressing smoking cessation, HPV vaccination, cervical cancer screening as part of an integrated cervical cancer prevention program disseminated by clinics. Delayed Arm health systems will initially enroll female smokers into an observational study, which will allow estimation of the smoking cessation rate in the target population receiving usual care. This group of women will serve as the comparison for the “effectiveness” of *Break Free*. After 12 months, while the Early Arm health systems are in the sustainability period, Delayed Arm health systems will implement *Break Free*, delivered by our research staff. After that 12-month period ends, they too will then shift to a sustainability period. Implementation of *Break Free* will be evaluated through randomly sampled patient assessments of provider fidelity to AAR and, for women enrolled in *Break Free* TTS counseling, assessments of TTS fidelity to *Break Free* counseling.

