## Limitations

Despite efforts to minimize bias, there are limitations to this planned study. First, results may be subject to observation bias, as clinics in this cluster randomized trial are unblinded after baseline assessment. Second, smoking behavior and cessation outcomes are measured by self-report, and participants’ responses may be influenced by social desirability. Self-report measures are a practical compromise. While biochemical validation or data from EHRs documenting smoking status would be considered a “gold standard” for tobacco studies, neither are especially practical for researchers or partner clinics. The *Break Free* study is designed to assess the effectiveness of a well-established intervention that combines behavioral counseling with pharmacotherapy. Also, biochemical verification of smoking status is not always needed in pragmatic randomized control trials [55] and has lower response rates than self-report data [56]. Third, missing data can be an issue in trials with longitudinal designs; however, the planned 6- and 12-month follow-up is consistent with current recommendations for smoking cessation studies [56] and the planned analyses will follow intent-to-treat methods to minimize bias from dropout over time. Finally, beyond collecting information about each clinic’s specific EHR, including any existing processes to identify tobacco users, clinic-level data on other variables that may affect implementation of *Break Free* (e.g., smoking rates of clinic providers and staff, access to smoking cessation for clinic employees) will not be collected in this study.

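### Women are recruited after open allocation and by different routes in each arm, and the lead Early–Delayed comparison is not adjusted for patient characteristics, so it is open to recruitment bias

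*Protocol article*

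**What the plan says.** The design section of the protocol article states that "health systems are stratified by state and then randomized in a 1:1 ratio to either an Early Arm or Delayed Arm", and that "Neither health systems nor study participants are blinded to their intervention assignment". During the first period, "Delayed Arm health systems will initially enroll female smokers into an observational study"; the same section makes these women the comparator for effectiveness.

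The patient criteria are listed once, under the Early Arm heading. The last three are "5) able to participate in phone counseling; (6) willing to try pharmacotherapy; and (7) not pregnant".

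In the Early Arm (Procedures), a provider advises the woman, prescribes and refers her. The Enrollment Specialist then gives her the materials, and the tobacco treatment specialist (TTS) telephones her for verbal consent and the baseline assessment. If she does not answer, "they will attempt to reach them up to ten times to schedule the informed consent and baseline assessment".

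In the Delayed Arm, providers question *eligible* female smokers, a word not defined for that arm. Then "Female smokers who are interested in quitting in the next 6 months will be asked to participate in this observational component of the study". Women who agree sign and complete a paper packet and post it, or use an online consent and survey. Delayed clinics take on the Early Arm procedures only when their own active phase begins.

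Under Statistical analyses, Patient outcomes, mixed models compare the arms at 6 and 12 months with no patient covariates named. After that, "Subsequent analyses will adjust for patient-level characteristics". The Limitations section says that "clinics in this cluster randomized trial are unblinded after baseline assessment" and does not mention recruitment bias.

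**The concern.** When clusters are randomised and patients are recruited later by staff who know the allocation, randomisation protects the comparison of clusters but not the comparison of the women enrolled. Here the filters also differ by arm. An Early woman is counted only if she accepted referral and answered the phone. A Delayed woman is counted only if she completed and returned a survey. If these filters pass women with different underlying chances of quitting, the arms differ at 6 and 12 months even if Break Free does nothing. Intention-to-treat analysis does not help, because it starts at enrolment, after the selection has taken place.

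The patient-outcomes section also counts survey non-responders as smokers. Under that rule, a difference between arms in how easily women can be contacted would feed directly into the apparent quit rates.

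**Working it through.** **1. Order of events, side by side**

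| Step | Early Arm | Delayed Arm (control period) |
|---|---|---|
| Allocation known to clinic | Before any woman is approached | Before any woman is approached |
| Written criteria | Seven, listed under this arm | *Eligible*, plus interest in quitting within 6 months |
| Before consent | Advice, prescription, referral, materials | Tobacco use and readiness asked |
| Gate to enrolment | Reached by TTS by phone, verbal consent | Packet posted back, or online form completed |
| Baseline | By phone, by the TTS | Self-completed |

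Whatever *eligible* means, the two gates differ and both come after open allocation.

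**2. The plan's own power figure**

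Inputs, from Sample size and power analysis: 10% against 25%, intraclass correlation 0.017, 43 women per system, 5 systems per arm, two-sided 5%.

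- Design effect = 1 + (43 − 1) × 0.017 = 1.714
- Effective number per arm = 5 × 43 / 1.714 = 125.4
- Standard error = √[(0.10 × 0.90 + 0.25 × 0.75) / 125.4] = √(0.2775 / 125.4) = 0.0470
- Ratio = 0.15 / 0.0470 = 3.19
- Power with a noncentral t on 10 − 2 = 8 degrees of freedom = 79.7%, against 80% stated

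The stated power is reproduced. A normal approximation gives 88–89%, so the t version is used below. The 8 degrees of freedom are my choice; the article does not print its formula.

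**3. Illustration: selection only, no treatment effect**

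The documents give no figure for a selection effect, so the excess *d* is an assumption. The Delayed rate is held at 10% and the Early rate set to 10% + *d*, with the same effective number. For *d* = 3 points, the standard error is √[(0.09 + 0.13 × 0.87) / 125.4] = 0.0402 and the ratio is 0.03 / 0.0402 = 0.75. For *d* = 5 points, they are √[(0.09 + 0.15 × 0.85) / 125.4] = 0.0416 and 1.20.

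| Assumed excess from selection | Two-sided rejection rate, t on 8 df | Normal approximation |
|---|---|---|
| 0 points | 5.0% | 5.0% |
| 2 points | 7.3% | 8.0% |
| 3 points | 10.1% | 11.6% |
| 5 points | 18.6% | 22.5% |

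With 51 women per system, 5 points gives 19.9% rather than 18.6%. A larger sample therefore does not remove the problem.

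**4. What imbalance would produce such an excess**

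Suppose a trait multiplies the odds of quitting and is more common among Early women, with the overall Delayed rate at 10%.

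- Odds ratio 2, trait in 50% of Delayed and 100% of Early women: quit rates are 7.0% without the trait and 13.0% with it. The excess is 13.0 − 10 = 3.0 points, and the rejection rate 10.2%.
- Odds ratio 3, same shares: excess 4.6 points, rejection rate 16.6%.
- Odds ratio 1.5, trait in 50% against 75%: excess 0.9 points, rejection rate 5.5%.

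A 3-to-5-point excess needs a marked imbalance in a strong predictor. A mild imbalance does little harm.

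**The case against.** **Do the entry criteria differ?** A reader might infer that they do. The documents do not establish this. The paragraph that lists the patient criteria also defines eligible health systems and providers in trial-wide terms, and it is the only definition of eligibility in the article. The word *eligible* in the Delayed text may well import the list, and its place under the Early heading may be only layout. The text is ambiguous on criteria 5 and 6. The different routes to enrolment remain on either reading.

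**Can the bias be sized and signed?** A reader might suppose that 20–40% of controls fail criteria 5 and 6 and quit 5–10 points less often. That would depress the Delayed rate by 0.20 × 5 = 1 point to 0.40 × 10 = 4 points, or 7–27% of the planned 15-point difference. None of these inputs is in the documents, and the result falls to about zero if the list applies to controls. Direction is not settled either: completing and returning a packet also selects motivated women, which would work against Break Free.

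**Is the Limitations sentence wrong?** Its subject is clinics, and the Break Free section describes clinic assessments in the year before launch, so a clinic-level baseline may be meant. That supports a request to reconcile, not a charge of error. On that reading, clinics would still know their arm before recruiting any woman.

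**Is adjustment not already planned?** It is, and the covariate names may properly stand in an analysis plan that is not shown. Their absence is no finding. What the article does fix is the order: the comparison without patient covariates comes first and the adjusted one is subsequent.

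**Is some asymmetry inherent?** Yes. Provider advice, prescription and referral are part of the intervention, so in the Early Arm they precede TTS consent by design. This limits what can be equalised and is a reason to disclose the remainder.

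**Conclusion.** The point holds in a limited form. Open allocation before recruitment, arm-specific routes to enrolment, and a lead comparison without patient covariates are all in the text. Together they leave the main effectiveness comparison open to recruitment bias, which the Limitations section does not acknowledge. Whether controls are screened for phone-counseling ability and willingness to try pharmacotherapy is unclear.

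The size of the bias cannot be derived from the documents. Its direction is uncertain, though phone reach and treatment willingness probably favour the Early Arm. The rise from 5% to about 10–19% in false positives rests on an assumed selective excess of 3 to 5 points, a 10% Delayed quit rate, 43 women per system, an intraclass correlation of 0.017 and a t test on 8 degrees of freedom. Under a normal approximation it would be about 12–23%. This does not invalidate the trial, but it affects how an observed difference can be read.

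**What to change.** 1. State that the listed patient criteria apply identically to Delayed Arm controls, and add two yes/no screening items to the Delayed baseline packet: able to take part in phone counseling, and willing to try pharmacotherapy.
2. Make the lead Early–Delayed model the one adjusted for prespecified baseline covariates: age, cigarettes per day, and readiness to quit (within 30 days against 1–6 months). Where possible, use values recorded at the clinic visit, because the Early phone baseline follows advice and prescription. Keep the unadjusted model as secondary. Do not use the two screening items as covariates if they are entry criteria, since every enrolled woman would then have the same value.
3. Report by arm the numbers eligible, approached or referred, reached, and enrolled.
4. Reconcile the Limitations sentence on unblinding with the design, Procedures and Delayed Arm sections. State post-allocation recruitment as a limitation that adjustment addresses only in part, because it corrects measured differences only and leaves the phone-contact filter in place.

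The cost is two survey items, one eligibility sentence, a change in model order and a revised limitation. The Delayed cohort would be slightly narrower and accrue somewhat more slowly. Asking usual-care women about willingness to use pharmacotherapy could also act as a small prompt.
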